## Abstract

**Background:**

Acutely ill and frail older adults and their next of kin are often poorly involved in treatment and care decisions. This may lead to either over- or undertreatment and unnecessary burdens. The aim of this project is to improve user involvement and health services for frail older adults living at home, and their relatives, by implementing advance care planning (ACP) in selected hospital wards, and to evaluate the clinical and the implementation interventions.

**Methods:**

This is a cluster randomized trial with 12 hospital units. The intervention arm receives implementation support for 18 months; control units receive the same support afterwards. The ACP intervention consists of 1. Clinical intervention: ACP; 2. Implementation interventions: Implementation team, ACP coordinator, network meetings, training and supervision for health care personnel, documentation tools and other resources, and fidelity measurements with tailored feedback; 3. Implementation strategies: leadership commitment, whole ward approach and responsive evaluation. Fidelity will be measured three times in the intervention arm and twice in the control arm. Here, the primary outcome is the difference in fidelity changes between the arms. We will also include 420 geriatric patients with one close relative and an attending clinician in a triadic sub-study. Here, the primary outcomes are quality of communication and decision-making when approaching the end of life as perceived by patients and next of kin, and congruence between the patient’s preferences for information and involvement and the clinician’s perceptions of the same. For patients we will also collect clinical data and health register data. Additionally, all clinical staff in both arms will be invited to answer a questionnaire before and during the implementation period. To explore barriers and facilitators and further explore the significance of ACP, qualitative interviews will be performed in the intervention units with patients, next of kin, health care personnel and implementation teams, and with other stakeholders up to national level. Lastly, we will evaluate resource utilization, costs and health outcomes in a cost-effectiveness analysis.

**Discussion:**

The project may contribute to improved implementation of ACP as well as valuable knowledge and methodological developments in the scientific fields of ACP, health service research and implementation science.

**Trial registration:**

ClinicalTrials.gov Identifier NCT05681585. Registered 03.01.23.

**Supplementary Information:**

The online version contains supplementary material available at 10.1186/s12913-024-10666-0.

## Background

The world’s population is rapidly ageing, requiring health systems to adapt to this population shift. Older adults represent a large proportion of hospitalized patients [1], they often have comorbid chronic illnesses and disability, and acute illness often comes with deterioration of physical health and cognitive function [2]. Overall health care and hospital utilization increase dramatically in the last months of life and a large proportion of old adults die in hospital [3–5].

It is well known that frail older adults and their relatives are often poorly involved in treatment and care decisions [6, 7]. At the same time, the communication between the service levels during admission and discharge is often deficient [8, 9]. This may lead to both over- and under treatment [7, 10] and considerable and unnecessary risks, burdens, distrust, conflicts as well as costs, for example because of undue hospitalization [10–13]. Advance care planning (ACP) is a well-documented tool to comply with the ethical and legal imperative to involve the patient and their relatives in the planning of current and preparing for future treatment and care [14]. ACP has its origins in the principle of respect for the patient’s autonomy and the right to self-determination [15]. It can be defined as the process of exploring the patient’s values and preferences for care and treatment at the end of life before decisions must be made [16]. ACP can improve quality of communication, prevent decisional conflict [17], improve health and satisfaction for patients and their relatives, and increase staff competence and confidence [11, 12, 18, 19].

Despite the evidence of the benefits of ACP and despite being key priority in national and international policies [16, 20–22], implementation is patchy [23], and ACP remains underused in the health care services [6]. A common strategy to facilitate the adoption of new practices is to develop guidelines [20]. Internationally, ACP guidelines exist [16, 20] but the gap between policies and practice remains large [6, 15]. Trials that include both implementation and intervention strategies to improve ACP in ordinary health care services can contribute to strengthen the pathway from guidelines to practice [24]. ACP is a complex intervention [25–27], and the full range of barriers and facilitators to implementing ACP have not been studied. Examples of barriers include reluctance and feeling of insecurity to talk about existential issues and the limits of medicine, poor communication skills, paternalism, specialisation, and fragmentation [7, 28]. There are also more general barriers to translating evidence into everyday clinical practice, such as lack of time [29] and commitment by leadership. Elements supporting successful ACP implementation [30] include whole-system approach, targeting multiple stakeholders concurrently (patients, caregivers, health care personnel), improved communication, application of guidelines, and skills training.

The Norwegian health and care services do well in international comparisons of quality of treatment, and Norway is also better equipped to meet the challenges of an ageing population than most other countries [31]. Important reasons for this are the Nordic welfare model and a strong economy. Although the health care services have become more patient-centered in recent years, ACP is, as in other countries, rarely implemented. ACP is to a certain extent in use in Norwegian nursing homes and in the palliative care setting, more seldom in other specialist and hospital care or primary health care. Advanced directive forms are little used, and neither advanced directives nor ACP are explicitly regulated by health legislation [32]. In general, we still lack evidence to answer the questions of timing, place and who should do ACP, to implement ACP on a large scale in routine services. There is evidence indicating that initiating ACP in nursing homes may be too late for the patient to be able to participate themselves [33–35]. For this study, we considered that it would be too challenging at the time being to implement ACP in primary health care outside nursing homes, and that available evidence was not sufficient for our study design. Through discussions with key stakeholders and based upon available evidence and knowledge of Norwegian health care services, we decided to focus on frail older home dwelling adults acutely admitted to hospital.

In this context, our project will—through the use of mixed methods and responsive evaluation—develop, put into practice and evaluate interventions to implement ACP in Norwegian geriatric units and medical wards with geriatric beds. We use a cluster randomized design to measure and compare changes and differences in implementation levels, health service outcomes and clinical outcomes for patients and next of kin between intervention- and control sites. Within this trial design, we employ formative evaluation to evaluate and improve the implementation processes, and we will use qualitative studies to investigate and explore the implementation process and the significance of ACP for central stakeholders in the participating geriatric units. We will also qualitatively explore key barriers and facilitators for ACP among stakeholders in a broader context, including other health care services and at the municipal, regional, and national level. A novel and comprehensive fidelity scale will be developed by the project group and used in the trial to assess the implementation level, penetration rate and the content and quality of the ACP in the intervention and control arm, and to guide the implementation strategy in the intervention arm. It will after the project be made available as a tool for coming research and quality improvement in the field.

The overall aim of the project is to improve health services, user involvement and patient-centered care for frail older adults and their next of kin, in an efficient, sustainable, and coordinated way, through better implementation of ACP.

## Objectives

### Primary objective

To evaluate whether the implementation support, relative to no support, is associated with improved implementation of ACP and with better involvement of patients and next of kin in geriatric units.

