### Secondary objectives

To measure the present level of implementation of ACP in all participating hospital units.To evaluate whether the implementation support, relative to no support, is associated with improved implementation of ACP, measured with the ACP fidelity scale (sum score, the quality subscale, the implementation subscale and the penetration rate subscale).To identify barriers to, facilitators for and experiences with implementing ACP among the stakeholders at the a) clinical, b) health care service- and c) municipal, regional and national level.To explore moral dilemmas and conflicting interests related to ACP, and strategies on how to resolve them.To explore benefits and disadvantages with ACP among patients and their next of kin, and to explore the benefits and disadvantages of both the implementation support and ACP among health care personnel and the implementation teams.To investigate whether the implementation support is associated with improved quality of communication and decision-making when approaching the end of life for patients and next of kin, better congruence between the patient’s preferences for information and involvement and the attending clinician’s perceptions of the same, and improvements of other relevant outcomes for patients, next of kin and the attending clinician.To assess whether higher level of implementation (fidelity) of ACP is associated with improved outcomes for patients, next of kin, the staff and the services.To measure, before and during the implementation process, health care personnel’s perceptions, attitudes, self-efficacy, confidence in, and experiences in relation to information giving and involvement of patients and next of kin.To measure healthcare utilization, costs, and the cost-effectiveness of the implementation and of ACP in the routine health care in hospital units.

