## Methods

### Trial design

The project is a multicentre cluster randomized controlled trial (CRCT). Each participating geriatric unit, with responsibility to provide medical care to acutely admitted older medical patients, constitutes one cluster and is the unit of randomization. Figure 1 gives an overview of the study design. The article conforms to the Standard Protocol Items: Recommendations for Interventional Trials (SPIRIT) [36] (Additional file 1), and the study results will reported in accordance with the Consort 2010 extension to cluster randomized trials. All methods carried out in the study will be performed in accordance with relevant guidelines and regulations.

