The primary outcomes for the clinical effectiveness study “The triadic sub-study with patients, next of kin and clinicians” are described under “outcomes”. The unit of analysis is the individuals recruited in each cluster. Since we have not found comparable studies that have published data on these instruments, we decided to use a 0.5 SD improvement (medium effect) when calculating the sample size. Based on a 0.5 SD increase in the primary outcome and an Intra-class Correlation Coefficient (ICC) of 0.05, we need 132 patients in each arm or 22 per cluster with six clusters in each arm to achieve 80% power to detect a difference in the primary outcome among patients, between groups with a certainty of 95%. Taking into account the possibility of patients in the control arm receiving ACP, and incomplete or missing data, we aim to recruit at least 35 patients per cluster. A similar power calculation with the same conservative assumptions has been done for the primary outcomes for next of kin and clinicians with the same results (35 next of kin and 35 clinicians per cluster).

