### Blinding

Due to the nature of the project, neither the units, the local leaders, the health care personnel nor the project’s researchers can be blinded to the hospital units’ allocation status. The project group is small, and the project’s researchers will contribute to all parts of the project, including developing the implementation program and providing the implementation support. This makes the researchers more familiar with and knowledgeable of all aspects of the units, which strengthens the tailoring of the intervention, and it improves the quality of the evaluation. On the other hand, having researchers evaluate the results of a program and the support they have provided themselves may lead to a risk of experimenter bias. This will be minimized by awareness of the risk of bias and by dividing the responsibility for the implementation and for the evaluation between different researchers. To prevent selection bias, patients and next of kin will not be informed about the hospital unit’s allocation status, but they may deduce this from the kind of treatment they receive. We assume that self-reported data and data collected from national registries to a low degree will be susceptible to bias.

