#### Data analysis

Demographic and clinical data about the patients will be used to assess whether the patients in the control and intervention units are comparable. In addition, the participating units will collect basic and anonymous clinical information about all patients admitted to the units at shorter random time periods, to get more information about the participant units and to compare the included patients with all admitted patients.

Number and percentages of invitation to and participation in ACP for patients and next of kin will be calculated and compared between intervention and control group. The primary statistical analyses will be the difference in mean outcomes between participants in the intervention and the control group using linear mixed effects models. The random part of the model will consist of random intercept for patient or relative identification nested within centre. Missing data will be handled by multiple imputation using predictive means matching with 100 imputed data sets.

If the analyses show differences in the intervention and control arm, we will perform analyses to assess if higher fidelity score (higher levels of implementation) is associated with improved outcomes for patients, next of kin, and clinicians. For the secondary outcomes, we will compute average outcomes and SD for the intervention and the control group and use the t-test to determine if there is a significant difference between groups.

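### The triadic comparison estimates the effect of completed ACP in supported units, not the effect of implementation support that the objectives name

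*Protocol article*

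**What the plan says.** Two objectives attribute patient and next-of-kin outcomes to the support. The primary objective is "To evaluate whether the implementation support, relative to no support, is associated with improved implementation of ACP and with better involvement of patients"; it also names relatives and places the question in geriatric units. The secondary objective for the triadic outcomes is "To investigate whether the implementation support is associated with improved quality of communication and decision-making when approaching the end of life", again for patients and next of kin.

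Under Trial design, each unit "constitutes one cluster and is the unit of randomization". Under The implementation strategies, only intervention units receive support during the 18 months.

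Entry to the triadic sub-study differs by arm:

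- **Both arms** (Inclusion criteria for patients): patient and relative would take part in ACP together if it were offered.
- **Intervention arm** (Exclusion criteria for patients): excluded if ACP with patient, relative and physician did not take place before discharge, or if the clinician in that conversation did not consent to the research.
- **Control arm** (same section): excluded if patient or relative could not have taken part in ACP during the stay, or if no attending clinician consented. No ACP has to occur.

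Under the triadic Data analysis heading, "The primary statistical analyses will be the difference in mean outcomes between participants in the intervention and the control group using linear mixed effects models". No section redefines this as an effect among ACP recipients, or provides for questionnaire data from eligible intervention-arm patients who did not have ACP.

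**The concern.** Holding an ACP conversation happens after randomization and is what the support is designed to increase. Using it as an entry condition in one arm takes the reach of the support out of the patient-level comparison. A willing and able patient whom a supported unit did not reach contributes nothing to the intervention mean. The same kind of patient in a control unit is counted.

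The risk lies in the conclusion. A positive triadic result would naturally be written up, in the words of the objectives, as support improving communication and involvement for patients in geriatric units. Yet the triadic mean would look the same whether a unit held ACP with few or with most of its eligible patients, provided that the recipients did equally well. Nor can the sample show benefit to patients without ACP, although The implementation strategies section cites a nursing-home study by the same team that saw improvement across whole units, including patients who were not offered ACP.

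**Working it through.** **1. The two quantities.** Take eligible patients who are willing and able. Let p be the share who complete ACP in supported units, M1 the mean outcome of those reached, M0 the mean of those in supported units who are not reached, and C the mean of willing and able controls.

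- Effect of support, as the objectives ask: p × M1 + (1 − p) × M0 − C
- Triadic contrast, as the entry rules give: M1 − C
- Difference between the two: (1 − p) × (M1 − M0)

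They agree only if every such patient is reached or if the unreached fare as well as the reached. If controls were matched perfectly to the patients whom support reaches, the contrast would be the effect in reached patients. That is still not support versus no support.

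**2. The plan's own sample size.** Inputs from Selection, allocation of clusters and sample size: "we decided to use a 0.5 SD improvement (medium effect) when calculating the sample size"; ICC 0.05; 22 per cluster; six clusters per arm; 80% power; 5% level, taken as two-sided.

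- Individually randomized: 2 × ((1.960 + 0.842)/0.5)² = 62.8, so 63 per arm
- Design effect: 1 + 21 × 0.05 = 2.05
- 63 × 2.05 = 129.2 per arm; 129.2/6 = 21.5, so 22 per cluster and 132 per arm

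The stated 132 reproduces. The problem is what the contrast estimates, not this arithmetic.

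**3. Illustration of size.** Assumptions not in the documents: reach p; 0.5 SD in recipients; no effect without ACP; no ACP in controls; no selection. The support-level effect is then p × 0.5 SD. At the recruitment target of 35 per cluster, the variance of the difference is (2/6) × (0.05 + 0.95/35) = 0.0257, so the standard error is 0.160 SD.

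| p | Effect of support | Contrast ÷ effect | Power, normal approximation | Power, t on 10 df |
|---|---|---|---|---|
| 1.0 | 0.50 SD | 1.0 | 88% | 80% |
| 0.8 | 0.40 SD | 1.25 | 70% | 62% |
| 0.5 | 0.25 SD | 2.0 | 34% | 29% |
| 0.3 | 0.15 SD | 3.3 | 15% | 14% |

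The normal approximation is the method that reproduces 132. The 10 degrees of freedom (12 clusters minus 2) are a choice made here. Both columns assume that all 35 per cluster are analysed, although the target includes an allowance for missing data.

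**The case against.** **The plan separates two questions.** It calls itself both an implementation and a clinical effectiveness study, with primary outcomes for each. Reach is measured on all 12 units through the penetration subscale of the fidelity scale, and the triadic analysis also compares ACP invitation and participation by arm. Measuring benefit in recipients and reach separately is a legitimate design. This stands, and it limits the point: a reader might infer that the trial never tests the support or ignores reach, and that is wrong. It does not remove the mismatch, because the objectives still word the patient outcomes as effects of support. The planned analysis relating fidelity to outcomes uses the same triadic sample, so unreached patients are absent there too.

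**Controls are filtered.** Unwilling and unable patients are removed from the control arm as well. This also stands: only willing and able patients who were not reached are treated unequally. But judged willingness and ability are not the same as having had ACP.

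**Selection bias.** A reader might infer that the result is shown to be biased, since "neither the units, the local leaders, the health care personnel nor the project’s researchers can be blinded to the hospital units’ allocation status". Selection is possible, but the documents give nothing from which to size it, and the point here holds without it.

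**Rescaling.** It is tempting to multiply the contrast by penetration. The documents do not support this:

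- Penetration is defined against everyone who could benefit, a wider group than consenting triads.
- The sample-size section allows for ACP in controls. With assumed shares of 0.5 (intervention) and 0.2 (control), an effect d of ACP and no effect without it, the contrast is (1 − 0.2)d = 0.80d. Multiplying by 0.5 gives 0.40d, against a support effect of (0.5 − 0.2)d = 0.30d.
- It assumes no effect without ACP, which the cited whole-unit finding contradicts.

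**Cost-effectiveness.** A reader might conclude that the planned ratio is wrong. Health economics counts the costs of ACP and of the hospital stay, much of which also arises per recipient, and cost-effectiveness of ACP itself is a stated aim. Scaling only the effect would put costs and effects on different bases.

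**Conclusion.** The mismatch is real and follows from the text alone. The objectives ask about support versus no support. The triadic primary analysis estimates the effect of completed ACP in supported units versus usual care, in patients judged willing and able. It cannot be reported as the effect of support on eligible patients.

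No firm size can be given. The overstatement of 1.25 to 3.3 times and the fall in power in the table are illustrations that rest on an assumed reach of 0.8 to 0.3 and on the other assumptions listed there. They should not be read as a finding that the trial is underpowered, since the sample size was set for the contrast actually sampled. The fidelity outcome, and with it the implementation half of the primary objective, is not affected.

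**What to change.** 1. In Secondary objectives and in the triadic Data analysis section, state that the triadic contrast estimates the effect of completed ACP in supported units versus usual care, in patients judged willing and able to take part.
2. Do not report it as the effect of implementation support on eligible patients.
3. Present it next to the ACP invitation and participation percentages by arm that the analysis section already plans, so that reach and benefit are read together.
4. In Health economics, describe the triadic effectiveness input as per ACP recipient.

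This costs wording only and needs no new data. The claim that can be made for support at patient level becomes narrower.

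Optional, if recruitment rules can still be changed (recruitment was about to start when the article was submitted): enrol eligible triads in both arms by the same criteria, whether or not ACP is held, and analyse by allocation. That would answer the primary objective directly, at the price of a diluted contrast and lower power. Under the assumptions in the illustration, with reach of 0.7 (0.35 SD), six clusters per arm cannot exceed about 77% power by the normal approximation, however many patients each recruits: the variance cannot fall below (2/6) × 0.05 = 0.0167, and 0.35/√0.0167 − 1.96 = 0.75. This is a trade-off for the investigators, not a requirement.
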